### Interventions

#### Control Group (UC)

Based on current guidance [1], participants in the control group will receive UC delivered by physicians experienced in CFS management. UC will include a baseline professional evaluation and structured education covering the nature of CFS, pacing and energy conservation, sleep hygiene, balanced diet, avoidance of overexertion and symptom-contingent activity escalation, and advice to avoid initiating Tuina, acupuncture, massage, or other traditional Chinese manual or physical therapies during the trial. This UC framework will be applied at all centers using the same written guidance document.

Symptom-directed treatment may be provided when clinically indicated for insomnia, pain, anxiety, depression, or other relevant symptoms. This may include prescription or nonprescription medications and individualized medical advice. Initiation or dose changes of medications and additional consultations will be permitted when clinically necessary, but the reason, drug name, dose, frequency, duration, and prescribing physician will be recorded in the electronic case report form. UC exposure will be recorded for both groups at each assessment visit using a structured UC log that captures medical advice, consultations, medications, self-management recommendations, and nonstudy therapies. Differences in UC exposure between the groups will be summarized, and sensitivity analyses may adjust for major concomitant medications or prohibited cointerventions if imbalances occur.

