### Blinding

Because Tuina is a manual therapy, neither participants nor therapists can be blinded to group allocation. This open-label design may introduce performance and expectation bias. Moreover, most efficacy outcomes, including the 11-item Chalder Fatigue Questionnaire (CFQ-11), Pittsburgh Sleep Quality Index (PSQI), HADS, SF-36, and EQ-5D-3L, are patient-reported; therefore, assessor blinding provides limited protection against bias for these self-reported outcomes. This limitation is explicitly acknowledged and will be mitigated by standardized participant instructions, equal assessment schedules, electronic or paper questionnaire completion before clinical discussion, and separation of treatment providers from outcome assessors.

Outcome assessors responsible for collecting data will be blinded to group allocation and will not participate in treatment. The CGI will be assessed by clinicians who are blinded to allocation whenever feasible. Independent statisticians will analyze data using masked group codes until the primary analysis is finalized. Participants will be instructed not to disclose treatment details to assessors during follow-up visits.

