### Data Analysis Plan

#### Analysis Populations

The primary efficacy analysis will be based on the modified intention-to-treat (mITT) population, operationalized as the full analysis set (FAS). The FAS will include all randomized participants with valid baseline CFQ-11 data who either receive at least 1 component of the allocated study management after randomization or provide at least 1 postbaseline CFQ-11 assessment. Study management refers to Tuina and/or usual care in the intervention group and usual care in the control group. Participants in the FAS will be analyzed according to their randomized allocation, irrespective of adherence, treatment discontinuation, number of completed sessions, protocol deviations, or concomitant care.

Participants who do not initiate any allocated postrandomization study management but provide valid postbaseline CFQ-11 data will remain in the FAS and will be analyzed according to randomized allocation. Postrandomization exclusions from the FAS will be limited to participants who withdraw consent for use of all data, have no valid baseline CFQ-11 data, are found after randomization to have a major eligibility error, or withdraw immediately after randomization before any study management and provide no postbaseline primary outcome data. All such exclusions will be documented before database lock and summarized in the participant flow diagram.

The per-protocol set (PPS) will include participants who complete at least 80% of the assigned intervention requirements, have week 8 primary outcome data, and have no major protocol violations. The safety set (SS) will include all randomized participants who receive at least 1 component of the allocated intervention or usual care and will be analyzed according to treatment actually received.

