### Missing Data

All missing data will be documented with reasons whenever possible and summarized by group and visit. No last-observation-carried-forward approach will be used. The primary MMRM analysis handles missing repeated outcome data through likelihood-based estimation under the missing-at-random assumption, using all available observed data. Multiple imputation by chained equations will be performed as a sensitivity analysis for the primary outcome and key secondary continuous outcomes when postbaseline data are missing. The imputation model will include treatment group, center, baseline stratification factors, baseline outcome values, observed postbaseline outcomes, demographic variables, and relevant UC or concomitant-treatment variables. At least 50 imputed datasets will be generated, and estimates will be combined using Rubin rules [28-30]. For the clinical response rate, response status will be derived from imputed CFQ-11 values in the MI sensitivity analysis; an additional conservative sensitivity analysis will classify participants with missing week 8 CFQ-11 data as nonresponders. If overall missingness exceeds 20% or differs between groups by more than 10 percentage points, additional sensitivity analyses using delta-adjusted pattern-mixture methods will be considered to assess departures from the missing-at-random assumption. Additionally, the robustness of the primary outcome will be assessed using the PPS population as a sensitivity analysis.

All statistical analyses will be performed using SAS version 9.4 (SAS Institute). Statistical significance is defined as a 2-sided *P*<.05.

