### Strengths and Limitations

The study has several strengths. First, to our knowledge, this is the first large-scale, multicenter randomized controlled trial to investigate the efficacy and safety of Tuina therapy for CFS. The study design incorporates several methodological strengths to ensure rigor. Second, building upon our preliminary single-center pilot work, we have optimized the intervention protocol. We extended the treatment duration from 4 weeks to 8 weeks and the session length to 30 minutes. This dose optimization aligns with the chronic nature of CFS and aims to induce more stable, long-term therapeutic effects. A major challenge in manual therapy trials is operator variability [32]. Third, we have implemented a strict quality control system, including a unified SOP, centralized practitioner training, systematic treatment logs, and regular fidelity monitoring. This ensures that the intervention is reproducible across different clinical centers and allows cointerventions and concomitant medications to be described and explored in sensitivity analyses. Fourth, this trial includes a 24-week posttreatment follow-up, enabling evaluation of durability.

Several limitations should be acknowledged. First, because Tuina is a manual therapy, participant and therapist blinding is infeasible [33,34]. This open-label design may introduce performance or expectation bias. To mitigate this, we have implemented a strict assessor-blinded design, where outcome evaluators and statisticians are unaware of group allocations. Second, the primary outcome (CFQ-11) and key secondary outcomes are patient-reported measures, which are subjective. However, these scales are validated and widely accepted in CFS research, and we have included the CGI to provide a clinician’s perspective. Third, the study population is limited to patients meeting the CDC 1994 criteria; future research may need to explore efficacy across different diagnostic definitions (eg, Institute of Medicine or NICE criteria) to enhance generalizability.

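### Adjusting for medications or cointerventions used after randomization, triggered by an arm imbalance, gives only weak evidence on robustness (minor)

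*Protocol article*

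**What the plan says.** The control-group section of the protocol article allows treatment during the trial in response to symptoms: "Symptom-directed treatment may be provided when clinically indicated for insomnia, pain, anxiety, depression, or other relevant symptoms". It adds that "Initiation or dose changes of medications and additional consultations will be permitted when clinically necessary". Exposure is logged over time: "UC exposure will be recorded for both groups at each assessment visit using a structured UC log". Table 1 places the usual-care (UC) log and the concomitant-therapy record at weeks 0, 4, 8, 20 and 32. After promising a summary of between-group differences in exposure, the section says that "sensitivity analyses may adjust for major concomitant medications or prohibited cointerventions if imbalances occur". It does not limit this to use before randomization, and it names no model, visit or estimand.

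Three other places bear on this:
- Blinding: "This open-label design may introduce performance and expectation bias".
- Analysis Populations: FAS participants are analyzed as randomized, "irrespective of adherence, treatment discontinuation, number of completed sessions, protocol deviations, or concomitant care".
- Strengths and Limitations: quality control "allows cointerventions and concomitant medications to be described and explored in sensitivity analyses".

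The primary model (Outcome Analysis) has baseline covariates only: center, the two stratification factors and baseline CFQ-11.

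**The concern.** The arms are randomized, so a later imbalance in medication or cointervention use arises either by chance or from the allocation. Both routes from allocation are plausible here. Use follows insomnia, pain, anxiety and depression, and the Discussion hypothesizes that Tuina improves sleep, mood and pain. Participants also know their arm, and this can change what they seek. The variable to be adjusted for can therefore be a consequence of treatment, and the imbalance trigger picks out the trials in which that is most likely.

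Conditioning on such a variable can remove part of the effect. It can also link arm to outcome through whatever drives both use and fatigue. If the adjusted figure is printed beside the primary one, a reader cannot tell whether a difference reflects the added therapy or the adjustment itself. What is at stake is the judgment of robustness, not the primary estimate.

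**Working it through.** **The plan's own figures.** For a difference of 3.0, SD 6.21 and two-sided 0.05, noncentral-t power is 0.8999 at 91 per group and 0.903 at 92. So 92 is the smallest n reaching 90%, and 92/0.8 = 115. These figures reproduce and are not disputed.

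**Inputs.** From the protocol: effect 3.0, SD 6.21, 92 per arm. Assumed, because the documents give none: use rate, correlations, and benefit of the added therapy. Reading the clause as a covariate in the outcome model is also an assumption.

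**Model.** S is improvement when use is decided and Y is improvement at week 8. Both have SD 6.21 and within-arm correlation ρ. Tuina shifts Y by 3.0, and shifts S by d = 1.5 (half) or 3.0 (full). Use follows a latent score with correlation k to S. With k = 1, everyone below a fixed improvement takes the therapy and nobody above it does; with k = 0.5, use follows response loosely. The use rate under UC is p0 and under Tuina p1. The added therapy improves Y by b. No baseline covariates are included.

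- z0 = Φ⁻¹(p0), z1 = z0 − k·d/6.21, p1 = Φ(z1)
- g = −ρ·k·6.21·[φ(z0) + φ(z1)] / [p0(1 − p0) + p1(1 − p1)]
- Adjusted contrast = 3.0 − g(p1 − p0), whatever b is
- Unadjusted contrast = 3.0 + b(p1 − p0)
- The two are equal at b = −g

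**Sharp cut-off, full shift, ρ = 0.5, p0 = 0.30.** z0 = −0.524 and z1 = −1.007, so p1 = 0.157. g = −0.5 × 6.21 × (0.348 + 0.240)/(0.210 + 0.132) = −5.33. Adjusted = 3.0 − 5.33 × 0.143 = 2.24.

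**Loose rule (k = 0.5), full shift, same ρ and p0.** z1 = −0.766, so p1 = 0.222. g = −0.5 × 0.5 × 6.21 × (0.348 + 0.298)/(0.210 + 0.173) = −2.62. Adjusted = 3.0 − 2.62 × 0.078 = 2.80.

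| Rule (ρ = 0.5, p0 = 30%) | Half shift: Tuina use, adjusted | Full shift: Tuina use, adjusted |
|---|---|---|
| Sharp, k = 1 | 22.2%, 2.59 | 15.7%, 2.24 |
| Loose, k = 0.5 | 25.9%, 2.89 | 22.2%, 2.80 |
| Looser, k = 0.3 | 27.5%, 2.96 | 25.2%, 2.92 |

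Under the sharp rule with 10% to 50% UC use and ρ from 0.3 to 0.7, the adjusted contrast runs from 2.86 down to 2.34 (half shift), or from 2.77 down to 1.69 (full shift). In simulation (92 per arm, 30% UC use, ρ = 0.5, inert therapy), the sharp rule lowers power from about 90% to about 85% (half) or 72% (full).

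**Direction.** Every adjusted value above lies below 3.0, the effect without added therapy. Against the effect regardless of use, the shift can go either way. With the sharp rule, full shift and p0 = 30%, the unadjusted contrast is 3.00/2.71/2.43/2.14 for b = 0/2/4/6. At ρ = 0.5, adjustment to 2.24 lowers it for b below 5.33 and raises it above that (2.14 to 2.24 at b = 6).

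A separate large simulation, with use driven by arm and in some scenarios by unmeasured severity, agrees:
- A therapy worth 2 points, used by 50% under UC and 27% under Tuina with no unmeasured severity, moves the benefit from 2.54 to 3.01.
- An inert therapy driven by unmeasured severity (50% and 30% use) moves it from 3.0 to 2.5.

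**When adjustment works.** If use depends only on arm and on a baseline severity that is in the model (35% and 24% use, 2-point benefit), large simulations return 2.98 to 3.01 against a true 3.0.

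**The case against.** The analysis is optional, applies only on imbalance, and is a sensitivity analysis whose stated role is exploration. No conclusion rests on it. This stands, and it sets the severity.

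The clause names no method. To adjust could mean weighting, or could be confined to the week 0 record, and an analysis plan not shown may say so. This stands in part: the figures hold only for the covariate reading. But the point is not absent detail. The text ties adjustment to an imbalance in exposure during the trial, and a prohibited cointervention is one begun after entry.

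The large shifts come from a deterministic cut-off with no baseline covariates. This stands. With k = 0.5 at ρ = 0.5 and full shift, the loss is 0.20 points rather than 0.76, about a quarter.

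A reader might infer that adjustment works only if use is unrelated to symptoms. That is too strong: it also works when the symptoms driving use are in the model, and the primary model already holds baseline CFQ-11 and the depression and physical-function strata. What those covariates cannot capture is response after baseline.

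The per-protocol analysis also selects on behavior after randomization. True, but that is a separate question and does not make this adjustment a better check.

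**Conclusion.** The concern holds at minor severity. As ordinary covariate adjustment, the permitted analysis targets neither the FAS effect nor, without a no-unmeasured-common-cause assumption that the protocol does not state, the effect without cointervention. Agreement or disagreement with the primary result is weak evidence on robustness.

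With 30% UC use, outcome correlation 0.5, true effect 3.0 and inert added therapy, the adjusted contrast runs from about 2.9 (loose, half shift) to 2.2 (sharp, full shift). The larger shifts and the power losses are upper-end cases, and all these inputs are assumed.

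A reader might infer that the primary week 8 result is at risk. It is not: its covariates are all baseline ones, and the FAS analysis ignores concomitant care. Nor do the response-driven calculations show error in both directions around the effect without added therapy. There, adjustment understates benefit; both directions appear only against the effect regardless of use. Including "relevant UC or concomitant-treatment variables" in the imputation model (Missing Data) is a different use of the same data and is acceptable.

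**What to change.** In the control-group section:

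- Keep the by-arm summary of UC exposure and tabulate it by visit.
- Limit simple covariate adjustment to use recorded at week 0. State that use after randomization is not entered as an ordinary covariate in outcome models, and that the FAS contrasts estimate the effect regardless of such use.
- If an effect without cointervention is wanted, define it as an exploratory hypothetical estimand. Either set data after cointervention to missing and multiply impute them from earlier scores, or use inverse-probability weighting. State the no-unmeasured-confounding assumption.

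The cost is a short wording change before recruitment. No new data collection is needed, since the log and therapy record are already scheduled, and the sample size, per-protocol analysis and imputation variables stay as they are. The downside is that no simple adjusted figure is reported. The optional estimand is also less precise, and it needs the symptom scores that drive use to be recorded before use starts. In an assumed simulation (sharp rule, 30% UC use, ρ = 0.5, single regression imputation as a stand-in), it averaged 2.96 to 3.02. Its standard error was about 1.03, against 6.21 × √(2/92) = 0.92 unadjusted.

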#### Intervention (Tuina Plus UC)

Participants in the Tuina group will receive the same UC framework in addition to the Tuina protocol.

### Practitioner Qualification and Training

Tuina will be delivered by licensed practitioners with at least 5 years of clinical experience. Before trial initiation, all practitioners will complete centralized training consisting of 4 two-hour sessions within 1 week. Training will include theoretical instruction, video demonstration, supervised hands-on practice, calibration of manipulation frequency and force, and review of the trial standard operating procedure (SOP). Practitioners must pass a competency assessment before treating trial participants.

### Standardized Tuina Protocol

#### Overview

An SOP will be strictly followed. The therapy will be administered 3 times per week for 8 consecutive weeks, totaling 24 sessions. Each session will last approximately 30 minutes. The protocol aims to regulate the spleen, liver, and kidney meridians by targeting specific regions and acupoints. The primary technique is pressing-kneading (An-Rou), supplemented by rolling (Gun), and pushing (Tui). The anatomical locations of the selected acupoints are shown in Figure 1.

**Figure 1. F1:**
[figure not shown]
Locations of the acupoints used in the Tuina protocol. (A) Anterior view showing the locations of Taiyang (EX-HN5) on the temples, Neiguan (PC6) on the forearm, Zusanli (ST36) on the lower leg, and Sanyinjiao (SP6) on the medial aspect of the leg. (B) Posterior view showing the locations of Baihui (GV20) on the vertex of the head, Fengchi (GB20) on the nape, Jianjing (GB21) on the shoulder, Pishu (BL20), Shenshu (BL23), and Weizhong (BL40) along the Bladder Meridian on the back and posterior leg. Image created with bioRender [19].

#### Head and Face (Supine Position, 6 Minutes)

Manipulation of the head and face in the supine position for 6 minutes.

Acupoints: *Taiyang* (EX-HN5), *Baihui* (GV20), *Fengchi* (GB20).Manipulation: The practitioner uses the thumb to apply pressing (An) and kneading (Rou) manipulations on these acupoints to tranquilize the mind. Each point is stimulated for approximately 2 minutes.

#### Upper Limbs (Supine Position, 2 Minutes)

Manipulation of the upper limbs in the supine position for 2 minutes.

Acupoints: *Neiguan* (PC6) bilaterally.Manipulation: Pressing-kneading is applied to *Neiguan* to regulate the heart and spirit. The practitioner also performs pushing (Tui) along the pericardium meridian on the medial side of the forearm.

#### Lower Limbs (Supine Position, 4 Minutes)

Manipulation of the lower limbs in the supine position for 4 minutes.

Acupoints: *Zusanli* (ST36) and *Sanyinjiao* (SP6) bilaterally.Manipulation: Pressing-kneading is performed on these points to strengthen the spleen and stomach, nourish *Yin*, and tonify *Qi*.

#### Back and Posterior Lower Limbs (Prone Position, 18 Minutes)

Manipulation of the back and posterior lower limbs in the prone position for 18 minutes.

Regions: The back, hips, and posterior aspect of the legs (along the Bladder Meridian).Acupoints: *Jianjing* (GB21), *Pishu* (BL20), S*henshu* (BL23), *Weizhong* (BL40), and *Ashi* points (tender points).Manipulation:Rolling (Gun): Applied along the Bladder Meridian on both sides of the spine (from the neck down to the lumbar region) to relax the paraspinal muscles.Pressing-kneading: Specifically applied to the focus acupoints to regulate visceral function.Pushing (Tui): Performed downward along the back and the posterior aspect of the legs to the heels to promote the flow of Qi and blood.

#### Treatment Regimen

##### Manipulation Parameters

Pressing-kneading will be maintained at approximately 120 repetitions per minute. During practitioner training and periodic quality checks, stimulation force will be calibrated using a pressure-measuring device or electronic scale, targeting an average force of 3.0 (SD 0.5) kg for pressing-kneading. Rolling will be performed rhythmically at approximately 120 to 160 oscillations per minute, and pushing will be performed at approximately 20 to 30 strokes per minute. Intensity will be adjusted to patient tolerance and reduced if discomfort exceeds 3 on a 0 to 10 numeric rating scale.

##### Intervention Fidelity

Practitioners will complete a treatment log after every session documenting date, duration, manipulation techniques, approximate force and frequency, deviations from the SOP, and adverse events. The coordinating center will review treatment logs regularly, observe or video-audit a random sample of sessions, and provide feedback or retraining if protocol deviations are identified. Participants who miss sessions will be contacted to encourage adherence, and missed sessions may be rescheduled within the 8-week treatment window when feasible.

### Outcome Measurements

#### Primary Outcome

The primary outcome is the change in fatigue severity from baseline to the end of the intervention (week 8). Fatigue severity will be measured using the CFQ-11 [20]. The CFQ-11 is a validated self-report instrument widely used to evaluate the degree of fatigue in clinical and epidemiological studies [21,22]. It consists of 11 items divided into 2 dimensions: physical fatigue (items 1‐7) and mental fatigue (items 8‐11). Each item is rated on a 4-point Likert scale (0=“less than usual,” 1=“no more than usual,” 2=“more than usual,” and 3=“much more than usual”). The total score is calculated by summing the scores of all items, ranging from 0 to 33. Higher scores indicate a greater severity of fatigue.

#### Secondary Outcomes

##### Clinical Response Rate

###### Overview

To evaluate the clinical significance of the treatment effect, the clinical response rate will be calculated at week 8. A responder is defined as a participant who achieves a reduction of ≥3 points in the CFQ-11 total score compared to baseline. This prespecified threshold was chosen as a conservative clinically meaningful improvement criterion informed by published work on minimal clinically important difference (MCID) for fatigue patient-reported outcome measures [23].

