## Introduction

Chronic fatigue syndrome (CFS), also known as myalgic encephalomyelitis (ME), represents a significant global health challenge, characterized by persistent or relapsing fatigue and a range of complex, medically unexplained accompanying symptoms [1,2]. The global prevalence of CFS is estimated to be between 0.4% and 2.6%, and incidence rates may be rising due to modern lifestyle stressors and postviral sequelae (eg, long COVID) [2,3]. Individuals with CFS or ME may experience difficulties in working, education, and mobility. In severe cases, their condition may confine them to bed and render them dependent on care [4]. Given its unclear etiology, curative treatments remain elusive [1,5-7].

The management of CFS has traditionally emphasized graded exercise therapy (GET) and cognitive behavioral therapy (CBT) [5-7]. However, the safety of these interventions has been questioned, leading the 2021 National Institute for Health and Care Excellence (NICE) guidelines to withdraw GET due to concerns over symptom exacerbation, and downgrade CBT to a supportive role [8,9]. These limitations highlight a critical unmet need for nonpharmacological interventions that are both effective and well tolerated.

Tuina is a traditional Chinese medicine external therapy based on the fundamental theories of traditional Chinese medicine. Through specific manipulations such as pressing, kneading, and pushing on the meridians and acupoints, Tuina aims to promote the flow of Qi and blood, thereby restoring physiological balance [10]. Emerging evidence suggests that Tuina is a promising approach for alleviating CFS or ME symptoms, showing potential benefits in reducing fatigue, improving sleep quality, and alleviating anxiety and depression [11-13]. In addition, a recent systematic review and meta-analysis of massage therapy for CFS reported improvements in fatigue symptoms and few adverse reactions, although the included studies were heterogeneous and generally limited in methodological rigor [14].

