**Inclusion criteria**
Diagnosis of chronic fatigue syndrome or myalgic encephalomyelitis according to the 1994 Centers for Disease Control and Prevention criteria [18], which includes the following:(1) persistent or recurrent fatigue lasting more than 6 months; (2) other organic diseases causing chronic fatigue must be excluded based on medical history, physical examination, or laboratory findings.The concurrent occurrence of at least 4 of the following 8 symptoms: (1) self-reported impairment in short-term memory or concentration; (2) sore throat; (3) tender cervical or axillary lymph nodes; (4) muscle pain; (5) multijoint pain without joint swelling or redness; (6) headaches of a new type, pattern, or severity; (7) unrefreshing sleep; and (8) post-exertional malaise lasting more than 24 hours.Age between 18 and 65 years (inclusive), with no gender restrictions.Willingness to participate in the study and capability to provide written informed consent.

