### Quality of Life

Health-related quality of life will be assessed using the SF-36 [25]. This instrument measures 8 domains of health status: physical functioning (PF), role limitations due to physical health (RP), bodily pain (BP), general health (GH), vitality (VT), social functioning (SF), role limitations due to emotional problems (RE), and mental health (MH). For each domain, item scores are coded, summed, and transformed onto a scale from 0 (worst possible health state) to 100 (best possible health state). This study will specifically focus on the PF and BP subscales to assess functional improvement. For the PF subscale used as a stratification factor, the 10 PF items will be summed as a raw score ranging from 10 to 30 and transformed using the formula PF = (raw score − 10)/20 × 100; therefore, possible PF scores occur in 5-point increments.

Additionally, the EQ-5D-3L will be used to evaluate health utility. It covers 5 dimensions: mobility, self-care, usual activities, pain or discomfort, and anxiety or depression. Each dimension has 3 levels: no problems, some problems, and extreme problems. The responses are converted into a single utility index using the Chinese population-based value set [26]. The scale also includes a EuroQol Visual Analogue Scale (EQ-VAS), where participants rate their overall health on a vertical scale from 0 (worst imaginable health) to 100 (best imaginable health).

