### Comparison With Prior Work

CFS creates a substantial burden on individuals and health care systems. As highlighted by the 2021 NICE guidelines, standard nonpharmacological interventions, such as GET, are no longer recommended due to safety concerns, while CBT is primarily supportive rather than curative [1,8,9]. This underscores the need for additional nonpharmacological approaches that are acceptable to patients and unlikely to exacerbate postexertional symptoms. Previous studies suggest that Tuina and related manual therapies may improve fatigue and accompanying symptoms [11-14,31], but the evidence remains limited by small samples, single-center recruitment, heterogeneous intervention protocols, and short-term follow-up [15,16]. The present trial addresses these gaps by using a larger multicenter design, a standardized treatment manual, centralized randomization, prespecified statistical methods, and longer follow-up.

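### Tuina is motivated partly by avoiding symptom exacerbation, but no worsening criterion is prespecified on the patient-reported scales, and the adverse event section names symptom change as a focus for usual care only

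*Protocol article*

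**What the plan says.** **Rationale.** The Introduction reports that a 2021 guideline led to a decision to "withdraw GET due to concerns over symptom exacerbation" and concludes that effective, well-tolerated non-drug options are needed. Comparison With Prior Work repeats the need for "additional nonpharmacological approaches that are acceptable to patients and unlikely to exacerbate postexertional symptoms". Principal Findings includes acceptable safety among the hypotheses.

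**Patient-reported scales.** Under Clinical Response Rate: "A responder is defined as a participant who achieves a reduction of ≥3 points in the CFQ-11 total score compared to baseline". The article adds: "This prespecified threshold was chosen as a conservative clinically meaningful improvement criterion". Under Quality of Life: "This study will specifically focus on the PF and BP subscales to assess functional improvement". Outcome Analysis compares CFQ-11 as an adjusted mean difference and the other continuous scales by t test or rank-sum test on change. No section defines a worsened participant.

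**Other routes by which worsening could appear.**
- CGI-I runs from 1 to 7, with a worse end, and is analysed as an ordinal outcome. Table 1 schedules the CGI at week 8 and early withdrawal only. The Blinding section makes its blinding conditional on feasibility.
- Adverse events cover any untoward occurrence, are collected in both arms at every visit from week 0, and are compared between arms.
- Safety and Adverse Event Reporting gives a different focus by arm: bruising, persistent local pain, abrasion and fainting for Tuina; medication side effects and symptom fluctuation for usual care.
- Intervention Fidelity has practitioners log adverse events after every Tuina session.

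**The concern.** Symptom exacerbation is a harm that the protocol itself raises against an earlier non-drug treatment. One would expect the plan to say how many patients in each arm got worse. On the scales collected identically in both arms, it counts individual change in one direction only. Everything else on those scales is a comparison of averages or ranks, which can favour Tuina while a minority deteriorates.

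The adverse event route does not fully close the gap. Symptom change is named as a focus only in the usual care arm, and the Tuina arm has up to 24 extra occasions for logging events. These asymmetries could push a comparison of reported worsening in either direction. At stake is how well a conclusion of acceptable safety would be supported on this particular harm.

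**Working it through.** **1. The plan's own figure.** Inputs from Statistical Analysis: difference 3.0, change-score SDs 6.02 and 6.39 (55 per group), two-sided 0.05, 90% power.
- Pooled SD = √[(54×6.02² + 54×6.39²)/108] = 6.208, stated as 6.21.
- Normal approximation: 2×(1.960+1.282)²×6.21²/3² = 90.05, so 91. The exact t calculation gives power 0.8999 at 91 and 0.9031 at 92, so 92.
- 92/0.80 = 115 per group, 230 in total. The figure reproduces and is not in dispute.

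**2. Classification under the responder rule.**

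| CFQ-11 change from baseline | Status |
|---|---|
| falls by 3 or more | responder |
| falls by 2 | non-responder |
| rises by 8 | non-responder |

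**3. Can the planned CFQ-11 summaries favour Tuina while more Tuina patients worsen?** Assumptions, not in the document except where noted: normal change; SD 6.21 within each component; usual care mean reduction 5.36 (pilot); Tuina mean reduction 5.36 + 3.0 = 8.36; worsening means a rise of 3 or more, mirroring the responder rule.

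For a component with mean reduction m: P(worsen) = P(Z > (3+m)/6.21) and P(respond) = P(Z > (3−m)/6.21).

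- *Usual care, m = 5.36:* worsen P(Z > 1.346) = 8.9%; respond P(Z > −0.380) = 64.8%.
- *Tuina, uniform benefit, m = 8.36:* worsen P(Z > 1.829) = 3.4%; respond P(Z > −0.863) = 80.6%.
- *Tuina, 20% worsen by a mean of 6:* the rest must improve by (8.36 + 0.20×6)/0.80 = 11.95 for the mean to stay at 8.36.
  - Worsen: 0.20×P(Z > −0.483) + 0.80×P(Z > 2.407) = 0.20×0.6855 + 0.80×0.0080 = 14.4%.
  - Respond: 0.20×P(Z > 1.449) + 0.80×P(Z > −1.441) = 0.20×0.0736 + 0.80×0.9252 = 75.5%.

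In the last case the mean difference is still 3.0 and the responder rate favours Tuina (75.5% versus 64.8%), yet 14.4% of Tuina versus 8.9% of usual care patients worsen by 3 or more. That is 0.144×115 ≈ 17 versus 0.089×115 ≈ 10 patients.

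**4. How precise would a count be?** For that case the risk difference is 5.4 points. With 115 per arm, SE = √[(0.144×0.856 + 0.089×0.911)/115] = 0.042, so the 95% CI is about −2.8 to +13.7 points. Power at 92 per group is 25% for 5% versus 10% and 62% for 5% versus 15%. The count is descriptive.

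**The case against.** **Stronger readings that the document does not support.** A reader might infer that the scales are read only for improvement, or that the trial cannot show whether patients got worse. Neither holds. Change scores are signed and tests are two-sided; CGI-I includes worse categories and is analysed ordinally; adverse events are broadly defined and compared between arms. The proposed count needs only data already scheduled. It would also be wrong to say that there is no randomized comparison of harm.

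**The rationale should not be overstated.** Exacerbation is one strand; the main stated gap is small, single-center, short-term and non-standardized evidence. CFQ-11 also does not measure post-exertional symptoms as such, so a CFQ-11 worsening count addresses fatigue exacerbation, not that narrower harm. This stands.

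**The illustration depends on its size.** If only 10% of Tuina patients worsen by a mean of 6, and the rest improve by (8.36 + 0.6)/0.90 = 9.96, 8.5% worsen in Tuina against 8.9% in usual care, and the between-arm count shows no excess. The 20% case also raises the Tuina change SD to √[6.21² + 0.20×0.80×(11.95+6)²] = 9.5, against a pilot value of 6.02. A spread that wide could be noticed in descriptive tables, although no planned rule reads it as harm. The case shows what is possible, not what is likely.

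**Deterioration tables often belong to the analysis plan.** That is fair, and a table may exist there. But the article itself fixes the responder rule and its threshold, and its adverse event wording differs by arm. That wording is present in the text and can be corrected there.

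**Conclusion.** The point holds as a modest improvement rather than an error in a figure. The article fixes an individual threshold for benefit on CFQ-11 and none for worsening on any patient-reported scale, while naming symptom change as an adverse event focus in one arm only. The remaining routes are real but limited: the CGI has one scheduled visit and conditional blinding, and its proportional-odds summary describes a common shift, which does not isolate a worsened minority; adverse event ascertainment is unequal between arms.

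In the 20% case, 14.4% versus 8.9% worsen while both planned CFQ-11 summaries favour Tuina. This rests on normal change, a component SD of 6.21, the pilot usual care mean and a mirrored 3-point threshold, which is an assumption. The sample size and primary analysis are unaffected.

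**What to change.** 1. Under Clinical Response Rate and Safety and Adverse Event Reporting, prespecify a descriptive safety outcome: the number and proportion per randomized arm whose CFQ-11 total rises by 3 or more points from baseline at weeks 4 and 8.
2. Because CFQ-11 stops at 33, anyone with a baseline above 30 cannot register a 3-point rise. Therefore also count a fall in SF-36 PF of a size fixed before data are seen, and a CGI-I rating of 6 or 7 at week 8.
3. Report risk differences with 95% CIs, without a confirmatory test.
4. In Safety and Adverse Event Reporting, state the symptom-worsening monitoring focus in the same words for both arms.

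A split by the entry symptom "post-exertional malaise lasting more than 24 hours" is optional and not part of the required change.

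**Cost.** A few tables from data already collected on the same schedule in both arms, and one sentence reworded. There is no extra visit, no sample-size change and no effect on the multiplicity plan. The downside is low counts and wide intervals, so the absence of a visible difference must not be read as evidence of no harm.
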